### Primary outcome

Total number of split test procedures for the corresponding POCT analysis performed by the practice in a four-month period. In a given month, a split test procedure should only be performed if the practice conducted the POCT analysis. The maximum number of possible split test procedures for a single analysis in a four-month period is four.

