### Statistics

Cross-sectional differences in the outcomes between allocation groups in the baseline period and each of the follow-up periods are tested by means of t-tests (primary outcome) and chi-square tests (secondary outcomes). In order to investigate the development of split test procedure adherence over the up to four periods relative to the (changing) intervention, Poisson (primary outcome) and logistic (secondary outcomes) regression is used with GEE methods to account for the repeated measurements. To identify predictors for adhering to split test procedure guidelines, adjusted effects for the GP and practice characteristics are estimated in multivariate Poisson (primary outcome) and logistic (secondary outcomes) regression analysis on the outcomes at selected periods. Beyond the direct comparison of the randomization groups in the first follow-up period, comparisons in further follow-up periods are done to investigate various forms of potential legacy effect, *i.e*., the effect of an intervention in periods where the intervention is discontinued. All statistical analyses are performed using SAS, version 9.2 (SAS Institute Inc, Cary, NC).

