### Power calculation

We used an estimate of a mean number of 1.5 INR split tests based on laboratory data from 2007 in order to ascertain the power of the study. Given a standard deviation of 1, a power of 90%, and an effect of 0.5, we estimated that 172 practices are to be included in this study.

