### Power calculation

We used an estimate of a mean number of one hemoglobin and/or glucose split test based on laboratory data from 2007 in order to ascertain the power of the study. Given a standard deviation of 1.25, a power of 90% and an effect of 0.5, we estimated that 266 practices are to be included in this study.

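### The single-period Poisson predictor models have no stated allowance for dispersion, and RCT B's baseline counts are overdispersed; with default standard errors these could be up to about 24% too small in RCT B

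*Protocol article*

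**What the plan says.** The Statistics section of the protocol article sets out three analyses.

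- **Comparison of allocation groups, period by period.** Differences "are tested by means of t-tests (primary outcome) and chi-square tests (secondary outcomes").
- **Development over the periods.** Poisson (primary outcome) or logistic (secondary outcomes) "regression is used with GEE methods to account for the repeated measurements".
- **Predictors of adherence.** Here "adjusted effects for the GP and practice characteristics are estimated in multivariate Poisson (primary outcome) and logistic (secondary outcomes) regression analysis". The timing of these models is given only by the phrase "on the outcomes at selected periods". The periods are not named, and neither a variance estimator nor a scale parameter is given.

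The primary outcome is a bounded count per practice: "The maximum number of possible split test procedures for a single analysis in a four-month period is four". For RCT B, the footnote to Table 1 recommends four tests for each of two analyses, haemoglobin and glucose. Table 1 gives the baseline mean (SD) as 1.07 (1.36) in RCT B and 0.35 (0.55) in RCT A.

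**The concern.** A Poisson model takes its standard errors from the assumption that, given the covariates, the variance equals the mean. If the true variance is larger, the estimated effects remain usable, but their standard errors are too small and their p-values too low. The article attaches to the repeated-measures model a method whose customary empirical variance guards against this. It attaches nothing comparable to the single-period predictor models, although its own Table 1 shows extra-Poisson variation in RCT B.

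At stake is the list of GP and practice characteristics reported as associated with adherence in RCT B. Some could be declared predictors more often than the nominal 5% when they have no association.

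**Working it through.** **The plan's own figure first.** The article gives no dispersion figure, but its sample sizes show how the planning SDs were used. For RCT B: "Given a standard deviation of 1.25, a power of 90% and an effect of 0.5, we estimated that 266 practices are to be included". With a two-sided 5% level (assumed; none is stated), n per arm = 2 × (1.96 + 1.2816)² × 1.25² / 0.5² = 131.3, so 132 per arm and 264 in all. The t-distribution version gives 133 per arm and 266, as stated. For RCT A (SD 1, effect 0.5) the same steps give 170 and 172, against 172 stated. The planning SDs are therefore SDs of the count per practice and can be set against the planning means.

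**Inputs from Table 1 (baseline).** RCT B: mean 1.07, SD 1.36, 146 of 286 practices with at least one split test. RCT A: mean 0.35, SD 0.55, 67 of 213 practices with at least one.

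**Formulas.** Dispersion φ = SD²/mean. Default Poisson SE divided by true SE = 1/√φ. Actual size of a nominal 5% test = 2 × [1 − Φ(1.96/√φ)].

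| | RCT B | RCT A |
|---|---|---|
| Variance | 1.36² = 1.850 | 0.55² = 0.3025 |
| φ | 1.850/1.07 = 1.73 | 0.3025/0.35 = 0.86 |
| √φ | 1.315 | 0.930 |
| Default SE / true SE | 0.761 (23.9% too small) | 1.076 (about 8% too large) |
| Size of a nominal 5% test | 13.6% | 3.5% |
| Zeros observed | 1 − 146/286 = 49% | 1 − 67/213 = 69% |
| Zeros under Poisson | exp(−1.07) = 34% | exp(−0.35) = 70% |

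Rounding in Table 1 moves φ in RCT B only between 1.71 and 1.75, and the understatement between 23.5% and 24.4%.

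**Planning inputs.** For RCT B, "We used an estimate of a mean number of one hemoglobin and/or glucose split test based on laboratory data from 2007" with SD 1.25 gives φ = 1.25²/1 = 1.56, so default SEs 20% too small. For RCT A, "We used an estimate of a mean number of 1.5 INR split tests based on laboratory data from 2007" with SD 1 gives φ = 1/1.5 = 0.67, so default SEs too large. Both agree in direction with Table 1.

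**Allowing for covariates.** The ratio 1.73 is marginal, while the model needs variance equal to mean given the covariates. If the covariates explain a share R² of the RCT B variance, φ becomes about 1.73 × (1 − R²):

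| R² | φ | SE too small by | Size |
|---|---|---|---|
| 0 | 1.73 | 24% | 13.6% |
| 10% | 1.56 | 20% | 11.6% |
| 20% | 1.38 | 15% | 9.6% |
| 30% | 1.21 | 9% | 7.5% |

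The problem disappears at R² = 1 − 1.07/1.85 = 42%.

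**Simulation.** Overdispersed (negative binomial) counts with mean 1.07 and variance 1.85, 286 practices, one balanced null covariate, 2,000 runs. A nominal 5% test rejected in 13.9% of runs with default Poisson errors, 5.3% with a Pearson-scaled variance and 5.4% with a robust variance.

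**The case against.** The strongest reply is that the article does not say the standard errors will be model-based. Poisson regression with a scaled or robust variance still fits its wording, and a condensed article may leave the variance estimator to a fuller document. This stands in part: a reader might infer that uncorrected Poisson has been specified, and the text does not establish that. What remains is that the article names a model whose default assumption conflicts with data it prints, and provides protection only for the neighbouring analysis.

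Four further points limit the size.

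- **Baseline only.** The periods to be analysed are unnamed, and dispersion under reminders is unknown. As an illustration, suppose one arm gains the planned 0.5 and the SD stays at 1.36. The pooled mean is then 1.07 + 0.25 = 1.32, φ = 1.85/1.32 = 1.40, the understatement about 15.5% and the test size about 10%.
- **Two analyses in one count.** The mean among RCT B practices with any test is 286 × 1.07/146 = 2.10, and Table 1's footnote refers to two analyses, so 1.73 appears to describe the haemoglobin and glucose total. If each were modelled alone, with equal margins and correlation ρ, the ratio would be 1.73/(1 + ρ): between 1.73 (ρ = 0) and 0.86 (ρ = 1). If the total is modelled, 1.73 stands.
- **RCT A.** A reader might extend the charge of over-liberal p-values to both trials. Table 1 does not support that: plain Poisson would be slightly conservative in RCT A.
- **Many predictors.** A reader might compound the 13.6% over five independent null predictors to get 1 − (1 − 0.136)⁵ = 52%. The article fixes no such number, and characteristics it collects, such as age and year of graduation, are not independent. That figure should not be used.

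The reach is also small. Neither research question concerns predictors, the randomised comparisons do not use Poisson standard errors, and a binary outcome recorded once per practice cannot be overdispersed, so the logistic predictor models are not touched.

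**Conclusion.** The point holds as a weakness in a secondary analysis. As worded, the single-period Poisson models make no provision for dispersion, and RCT B's baseline counts do not meet the default assumption; the variance ratio, the excess of zeros and the planning inputs agree on this.

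The figures of 24% and 13.6% are what default errors would give in RCT B if baseline dispersion carries over, the combined count is modelled and the covariates explain almost nothing. They are best read as near the upper end, not as an established error. In RCT A the same default would make the errors about 8% too large. No conclusion on the efficacy or legacy of the reminders depends on this.

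**What to change.** State that the single-period Poisson predictor models in both RCTs use a robust (sandwich) variance or a Pearson-scaled dispersion parameter. In the SAS version already named this is one option or statement in the GENMOD procedure (PSCALE or REPEATED).

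One rule then serves both trials, correcting errors that are too small in RCT B and too large in RCT A. A negative binomial model for RCT B is not recommended: it cannot represent variance below the mean, as seen in RCT A, so it could not be the common rule.

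Point estimates do not change. The only cost is wider intervals in RCT B, by up to about 31% (√1.73 = 1.31) at baseline dispersion with uninformative covariates. RCT A intervals would become about 7% narrower (√0.86 = 0.93).

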### RCT A: Comparing computer reminders with postal reminders

Included in RCT A are the practices conducting more than four POCT INR during the four-month baseline period (213 practices). Practices are randomly allocated to computer-generated postal reminder letters or to ComRem; both in addition to usual laboratory quality guideline activities. The comparison of outcomes after a first follow-up period: the intervention period estimates the relative efficacy of ComRem over postal reminder letters; a comparison after a second follow-up period in which both interventions are discontinued estimates the relative legacy effect of the interventions.

## Intervention

### Postal reminder letters

In this group, computer-generated postal reminder letters are sent to practices not adhering to the guideline recommendations of split testing within the previous calendar month. Thus, practices may receive up to four postal reminder letters during each four-month follow-up round. The contents of the reminder are presented in Figure 1.

**Figure 1 F1:**
[figure not shown]
**Contents of reminder (RCT A)**.

### ComRem

In this group, ComRem are sent to practices not adhering to the guideline recommendations of split testing within the previous calendar month. Thus, practices may receive up to four ComRem. These reminders have exactly the same content as the postal reminders.

### Outcomes

The outcomes specified previously address the conduct of POCT for INR. The study period comprises three four-month periods: The baseline, the intervention, and follow up period.

### Power calculation

We used an estimate of a mean number of 1.5 INR split tests based on laboratory data from 2007 in order to ascertain the power of the study. Given a standard deviation of 1, a power of 90%, and an effect of 0.5, we estimated that 172 practices are to be included in this study.

### RCT B: Comparing computer reminders with usual activities and the potential legacy of electronic reminders

Included in the study are the 286 general practices conducting at least four POCT (either hemoglobin or glucose) during the four-month baseline period and that are not already included in RCT A. Practices are allocated to ComRem together with usual laboratory EQA practice or usual laboratory EQA practice only. The comparison of outcomes after a first follow-up period, the intervention period, estimates the relative efficacy of ComRem versus usual care only; a comparison after a second follow-up period in which the interventions are switched between groups estimates the relative efficacy of a (short-term) legacy effect of ComRem over the direct effect of ComRem; a comparison after a third follow-up period in which both interventions are discontinued estimates the relative efficacy of a long-term legacy effect of ComRem over the short-term legacy effect of ComRem.

## Intervention

### ComRem

Computer reminder letters are sent to practices not adhering to the guideline recommendations of split testing for either hemoglobin or glucose within the previous calendar month. Thus, all practices may receive up to four electronic reminder letters in each period. The content of the reminder is identical to the one in RCT A, except that this reminder addresses hemoglobin/glucose and not INR.

### Outcome

The outcomes specified previously address the conduct of POCT for hemoglobin and glucose. The study period comprises four four-month periods: The baseline, the intervention, cross-over, and follow up period.

### Power calculation

We used an estimate of a mean number of one hemoglobin and/or glucose split test based on laboratory data from 2007 in order to ascertain the power of the study. Given a standard deviation of 1.25, a power of 90% and an effect of 0.5, we estimated that 266 practices are to be included in this study.

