### Randomization

Within each study, practices are randomized into two similarly sized groups by means of computer generated random numbers using SAS version 9.2. To ensure that practice types are distributed equally over the intervention and control arms, randomization within each RCT is done separately for group practices and solo practices respectively. This randomization was conducted by the data manager of the Research Unit of General Practice without knowledge of the individual practice identification.

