## Results

A total of 567 practices with a total of 739 GPs were eligible in the study area with a total population of 1.1 million. In total, 213 practices were included in RCT A and 286 were included in RCT B (Figure 2). The characteristics of GPs and practices are presented in Table 1. Split tests were in general infrequently used by the practices (Table 1).

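### RCT B's 90% power rests on a 2007-based SD of 1.25; at the trial's own baseline SD of 1.36 the 286 included practices give about 87%

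*Protocol article*

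**What the plan says.** The Power calculation section for RCT B takes its planning mean from older data: "We used an estimate of a mean number of one hemoglobin and/or glucose split test based on laboratory data from 2007". It then sets the remaining inputs and the result: "Given a standard deviation of 1.25, a power of 90% and an effect of 0.5, we estimated that 266 practices are to be included". Neither alpha nor an allowance for dropout is stated there. The Discussion says that a power analysis was hard to do at the design stage, and that it drew on a 2007 laboratory report and experience with postal reminders.

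The Results section gives the final inclusion: "213 practices were included in RCT A and 286 were included in RCT B". Under Randomization, "practices are randomized into two similarly sized groups", so about 143 per arm in RCT B.

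Table 1 reports the RCT B primary outcome at baseline (combined hemoglobin and glucose split tests, January to April 2010) as mean 1.07, SD 1.36. The Statistics section tests the primary outcome between groups in each period with t-tests. Separately, it uses Poisson regression with GEE to follow adherence over the periods.

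**The concern.** The article gives two SDs for what is in effect the same quantity: 1.25 as the planning value and 1.36 as observed in the trial's own practices over a four-month window. The observed mean of 1.07 agrees well with the planning mean of one; the SD does not agree, and the power statement was left as it was.

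A reader who sees 286 practices against a target of 266 would conclude that RCT B exceeds its 90% target, at about 92%. At the observed SD it falls a little short of 90%. If RCT B shows no difference, the stated 90% is the figure readers will use to judge how firmly a difference of 0.5 has been ruled out.

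**Working it through.** **Inputs**
- Difference 0.5, planning SD 1.25, target power 90%, stated total 266: RCT B Power calculation.
- Observed SD 1.36, mean 1.07: Table 1.
- 286 practices: Results. Equal allocation: Randomization.
- Unadjusted two-sample t-test: Statistics.
- Assumed: alpha 0.05 two-sided; no dropout.

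**Step 1. Reproduce the stated 266.** Normal approximation, per arm: n = 2(1.960 + 1.282)² × SD² / difference².
- SD 1.25: 2 × 10.507 × 1.5625 / 0.25 = 131.3, so 132 per arm, 264 in total.
- With the t distribution, 132.3 per arm, so 133 per arm and 266 in total. This matches.
- One-sided 5% gives 216 and does not match, so two-sided 5% is the natural inference.

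**Step 2. Put in the observed SD.** The noncentrality is 0.5 / (SD × √(2/n)); with SD 1.36 and n = 143 it is 0.5 / (1.36 × 0.1183) = 3.11. Power from the noncentral t:

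| Total practices | SD 1.25 | SD 1.36 |
|---|---|---|
| 266 | 90.1% | 84.8% |
| 286 | 92.1% | 87.2% |

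At SD 1.36, 90% power needs 156.4 per arm, so 157 per arm and 314 in total (312 by the normal approximation).

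**Step 3. Express the gap in other units.** With 286 practices and SD 1.36, 90% power is reached at a difference of 0.523 instead of 0.50. The largest SD that keeps 90% for a difference of 0.5 with 286 practices is 1.30. A normal-theory 95% interval for the SD, from 286 practices with an estimate of 1.36, is about 1.26 to 1.48.

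**Step 4. Adjust for the baseline count.** With baseline to follow-up correlation r, the residual SD is 1.36 × √(1 − r²). Power with 286 practices and a difference of 0.5:
- r = 0.2: residual SD 1.33, power about 89%.
- r = 0.3: residual SD 1.30, power about 90%.
- r = 0.5: residual SD 1.18, power about 95%.

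The article gives no r, so these values are assumptions.

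**Step 5. How far the follow-up SD could move.** The article gives no follow-up SD. All figures below use 286 practices and a reminder-arm mean of 1.07 + 0.5 = 1.57.
- Variance proportional to the mean: the ratio is 1.36² / 1.07 = 1.73, so the reminder-arm SD is √(1.73 × 1.57) = 1.65, the pooled SD is 1.51 and power is about 80%.
- Gain made by practices that had no split test. Table 1 shows 146 practices with at least one, so 286 − 146 = 140 (49%) had none. If a quarter of all practices move from 0 to 2, the mean rises by 0.25 × 2 = 0.5. The reminder-arm variance is 1.36² + 1.07² + 0.25 × 4 − 1.57² = 1.53, so its SD is 1.24, the pooled SD is 1.30 and power is 90%.
- The same gain from one sixth of practices moving from 0 to 3 gives about 86%; from one eighth moving from 0 to 4, about 81%.

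**The case against.** The strongest reply is that a sample-size calculation is a statement about its own assumptions. The article labels its source as 2007 data, admits the difficulty, and prints the 2010 SD openly. That stands against any charge of miscalculation: a reader might infer from the mismatch that 266 is an arithmetic error, and it is not.

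The second reply is that the gap is small. Because 286 practices were included, the 85% figure describes a smaller trial than the one being run. The relevant loss is about 3 points, or about 0.02 of a split test in detectable difference, and the SD of 1.30 that would preserve 90% lies inside the sampling uncertainty of the observed SD. This also stands and limits the weight of the point. It does not make 1.25 the better planning value: that lies just below the interval in Step 3, and 1.36 is the best estimate from the trial's own practices.

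A third reply is that the t-test is not the only planned analysis, since the GEE Poisson model also uses the baseline period. That is true, but the article gives no power for that model, and 266 is reproduced by a plain two-sample comparison.

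A stronger reading is tempting: counts usually become more variable as their mean rises, so true power would be about 80%. The documents do not support that as a finding. Reminders go only to practices that missed the previous month, about half of practices started at zero, and each analysis is capped at four split tests per period. Step 5 shows that plausible patterns of response give anything from about 80% to 90%.

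**Conclusion.** The point holds as an outdated planning input with a modest effect. Under the planned unadjusted t-test, at the article's own baseline SD, RCT B has about 87% power for a difference of 0.5 with the 286 practices included, not 90% or the 92% that the surplus over 266 would suggest. With the 266 planned it would have been about 85%.

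This rests on two-sided 5% (inferred), equal arms, no loss of practices, and a follow-up SD equal to the baseline 1.36 in both arms. The last assumption could fail in either direction. A 3-point difference would not by itself lead anyone to misread a null result badly; the reason to act is that the correct figure is available from the article and the correction is cheap.

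**What to change.** 1. Add to the RCT B power section that, at the observed baseline SD of 1.36, 286 practices give about 87% power for a difference of 0.5 under the unadjusted t-test at two-sided 5%, and 90% for a difference of about 0.52. Keep the 266 as the original design calculation, labelled with its 2007 basis, and state alpha.
2. Adjust the first follow-up comparison for each practice's baseline split-test count, and report the power on that basis: about 90% if the correlation is about 0.3 or more, marked as an assumption.
3. If a figure for changed follow-up variance is wanted, give it as a sensitivity range (about 80% if variance rises in proportion to the mean, 90% if the gain comes from practices moving from none to two), and do not present it as the restated power.

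The cost is a sentence or two with a slightly less favourable number, plus one covariate that is already collected. No extra enrolment is needed: RCT B takes the practices that meet the test threshold and are not in RCT A, so its size is set by eligibility.

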### Ethics

This study uses blood samples that are not retraceable to specific patients in order to conduct the split tests. Patient identities are kept hidden through an artificial identification code used by all practices. The project has been evaluated by the Scientific Ethical Committee for Copenhagen and Frederiksberg Municipalities (j. nr. H-1-2010_FSP/10) and the Danish Data Protection Agency (j. nr. 2010-41-4680). The Danish College of General Practitioners Study Committee evaluated the project (MPU 12-2010). The two RCT are registered in ClinicalTrials.gov Identifier (NCT01152151, NCT01152177).

